### 2.1. Design

This is a two-arm parallel-group feasibility RCT, in which families will be randomly assigned to an intervention arm and a waitlist control arm, with a 1:1 allocation ratio. Parents in the intervention group will participate in the Being a Parent program, while the waitlist control group will not receive any intervention during this phase but will be given the opportunity to participate in the program after post-intervention assessments are conducted. Two outcome assessments will be completed by both arms at baseline and post-intervention, and an additional 6-month follow-up will be conducted only with the intervention arm, as assessing the control group at this stage would not provide accurate control data for comparison since the control group will have been participating in the Being a Parent program. Concurrently, a qualitative process assessment will be performed using semi-structured interviews to thoroughly explore the experience of the families who participated in the Being a Parent program, independently of their designated trial group. Figure 1 summarizes the participant flow throughout the study. As illustrated, parents will be recruited through different channels and will be asked to sign in through our website. If included in the study, participants will complete baseline assessments and proceed to randomization to either an intervention group or a control group. Post-intervention assessments will be completed by both groups, and the intervention group will have an additional 6-month assessment. Qualitative assessments will also be conducted.

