### 2.6. Measures

#### 2.6.1. Feasibility, Fidelity, and Acceptability

Structured sheets will be used to record significant feasibility parameters associated with trial methodology and program implementation. This will enable the assessment of participants’ rates related to (a) enrolment; (b) eligibility; (c) intervention attendance and retention; and (d) data collection. Dropout will also be recorded for both arms, as well as missed sessions for the experimental group. The research team, with the help of the group leaders, will fill out weekly review forms to assess fidelity criteria (e.g., the delivery of content; alignment with intervention methods and strategies). In addition, a treatment acceptability rating scale (TARS) created by the Empowering Parents, Empowering Communities team will be completed by the participants from the experimental group post-intervention. This scale was specifically created in order to assess the unique aspects of treatment acceptability that are specific to the Being a Parent program. It comprises 12 tailored items in which parents will report on satisfaction with intervention delivery. Questions reflect the content and delivery style of this specific parenting program, ensuring that the assessment is both contextually relevant and comprehensive (e.g., “*In general, are you satisfied with group leaders?*”).

A qualitative semi-structured interview will also be conducted post-intervention with a small sample of the participants from the experimental group. The main goal is to better understand the experiences of parents that participate in the parenting program. Therefore, topic guides will include open prompts regarding (a) trial implementation (e.g., recruitment and data collection); (b) intervention implementation (e.g., localization and dates); (c) intervention acceptability (e.g., content and impact); and (d) the adequacy of group leaders (e.g., competencies).

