### 2.7. Sample Size

Sample size calculation was based on the CONSORT 2010 statement extended to feasibility trials [35] and the Lewis et al. [36] methodology. This approach calculates sample size by conducting hypothesis testing based on estimations of predefined feasibility outcomes being within the unacceptable “red zone” (null hypothesis) and contrasting this with an alternative hypothesis of being within the “favorable” green zone [35]. A sample size is considered appropriate if it allows for ≥80% power to reject being in the red zone if the green zone holds true. For detailed information about this methodology, please consult Lewis et al. [36].

Progression parameters and their subsequent point estimates as described in Table 2 were used. Considering a one-tailed, one-sample binomial test based on normal approximation (with continuity correction) with α = 0.05, the following minimum sample sizes for each parameter were obtained:Feasibility of participant retention at post-intervention (Rul = 0.50 and Gll = 0.70)—41 participantsFeasibility of consent rate (Rul = 0.40 and Gll = 0.60)—42 participantsFeasibility of program completion (Rul = 0.45 and Gll = 0.75)—18 participants (intervention arm)Feasibility of program acceptability (Rul = 0.45 and Gll = 0.75)—19 participants (intervention arm)Feasibility of program fidelity (Rul = 0.40 and Gll = 0.70)—19 participants (intervention arm)

Therefore, a sample size of 42 participants, with 25 participants in the intervention arm, allows for ≥80% power to reject the null hypothesis for each of the feasibility outcomes. Moreover, this sample size is sufficient for the estimation of effect sizes for a future larger trial, as it allows for the collection of preliminary data needed to calculate reliable effect size estimates and assess the variability in psychological measures.

Regarding our qualitative data, according to the recommendations of Boddy [37] and van Risjnsoever [38], we aim to recruit 10 to 12 participants, as this sample size is often sufficient to achieve data saturation when the aim is to explore shared experiences within a relatively homogeneous group. Moreover, we will closely monitor data saturation during analysis and will adjust the sample size if necessary to ensure robust and meaningful findings.

**Table 2 healthcare-13-00176-t002:** Feasibility progression parameters.

Parameter	Thresholds		Justification

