1. Feasibility of Retention of Families at Post-Intervention *Can a significant number of recruited families be retained until post-intervention?*	GREEN ZONE (Go—Proceed with full RCT)	>70%	Ensuring a substantial post-intervention retention rate is essential to obtain accurate and unbiased post-intervention data Favorable retention rates at the feasibility trial will contribute to estimating the required sample size for a larger RCT Systematic reviews have shown that attrition rates between 9 to 27% can be found in RCTs testing parenting interventions for childhood behavior problems [39] Previous trials of the BaP program reported an average retention rate of 80% [18,19]
	AMBER ZONE (Amend—Proceed with changes)	50–70%	
	RED ZONE (Stop—Do not proceed unless significant changes are made)	<50%	
2. Feasibility of Consent Rate *Is the rate of eligible families who consented and were randomized favorable for a large-scale RCT?*	GREEN ZONE (Go—Proceed with full RCT)	>60%	An adequate consent rate is essential for the feasibility trial to accurately estimate the number of families who need to be reached, in order to achieve the required sample size to obtain significant statistical power in a large-scale RCT. Low consent rates may provide important information regarding issues in recruitment procedures (such as locations of recruitment or information available to interested participants). Previous trials report an average consent rate of 70% [40] Previous trials of parenting interventions in Portugal report consent rates ranging from 63% to 97% [41,42] Previous studies of the BaP program report an average consent rate of 71% [19]
	AMBER ZONE (Amend—Proceed with changes)	40–60%	
	RED ZONE (Stop—Do not proceed unless significant changes are made)	<40%	
3. Feasibility of Program Completion *Can a significant number of participants from the intervention arm complete the BaP program?*	GREEN ZONE (Go—Proceed with full RCT)	>60%	Achieving favorable program completion rates is critical to obtain accurate and unbiased data A systematic review [43] found a mean program completion rate of 80% with a wide variety across studies between 50% and 100% Previous trials of the BaP program have shown an average completion rate of 70% [18,19]
	AMBER ZONE (Amend—Proceed with changes)	30–60%	
	RED ZONE (Stop—Do not proceed unless significant changes are made)	<30%	

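### Retention is judged on one rate pooled over both arms; a Go verdict can hide heavy loss in one arm, so a simple arm-level check should be added

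*Protocol article*

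**What the plan says.** Table 2, parameter 1, asks: "Can a significant number of recruited families be retained until post-intervention"? It sets one scale: above 70% Go, 50–70% Amend, below 50% Stop. The first justification listed is "Ensuring a substantial post-intervention retention rate is essential to obtain accurate and unbiased post-intervention data".

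No arm is named. Parameter 3, by contrast, is confined to one arm: "Can a significant number of participants from the intervention arm complete the BaP program"? The sample-size list in section 2.7 shows the same contrast. Completion, acceptability and fidelity are marked as intervention-arm quantities; retention (41 participants) and consent (42) are not. Retention is therefore one rate over both arms.

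Section 2.6.1 says "Dropout will also be recorded for both arms", but no threshold uses the arm-level figures. The data that retention protects go into an ANCOVA comparing intervention with waitlist (section 2.8.1).

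On arm sizes, section 2.1 states 1:1 allocation, while section 2.7 concludes with "a sample size of 42 participants, with 25 participants in the intervention arm", which leaves 17 for the waitlist.

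**The concern.** The criterion is meant to protect a between-arm comparison, but it measures total loss. A pooled rate of about 71% is the same number whether each arm kept 71% or one kept 48% and the other 95%. The second case is far worse for the comparison.

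Unequal loss is plausible in this design. Waitlist families "will be given the opportunity to participate in the program after post-intervention assessments are conducted", which gives them a reason to return the questionnaires, and they have no sessions to drop out of. Intervention families are asked to attend eight weekly sessions, and Table 2 treats completion of 30–60% as amber.

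At stake is whether a full trial is judged ready on retention when its effect estimate would rest on about half of one arm and nearly all of the other.

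**Working it through.** **1. The plan's own figure.** Section 2.7: "Considering a one-tailed, one-sample binomial test based on normal approximation (with continuity correction) with α = 0.05", with the power requirement "A sample size is considered appropriate if it allows for ≥80% power to reject being in the red zone if the green zone holds true". Inputs for retention: p0 = 0.50, p1 = 0.70, z = 1.645 and 0.842.

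- Without correction: n0 = [(1.645·√(0.5·0.5) + 0.842·√(0.7·0.3)) / 0.20]² = 36.49.
- With continuity correction: n = (n0/4)·[1 + √(1 + 2/(n0·0.20))]² = 41.34.

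The article states 41; rounding up would give 42, the size adopted. The figure is reproduced to rounding, and it is a calculation for one pooled sample.

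**2. Which splits give Go.** Go needs a pooled rate above 70%. Of 42 that is at least 30 retained (30/42 = 71.4%; 29/42 = 69.0%). Of 50 it is at least 36 (72%). One unit per family is assumed, since Table 2 counts families and the sample size counts participants.

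| Arms (intervention:waitlist) | Waitlist retained | Lowest intervention count giving Go |
|---|---|---|
| 21:21 | 21/21 (100%) | 9/21 (42.9%) |
| 21:21 | 20/21 (95.2%) | 10/21 (47.6%) |
| 21:21 | 19/21 (90.5%) | 11/21 (52.4%) |
| 25:25 | 24/25 (96%) | 12/25 (48%) |
| 25:25 | 23/25 (92%) | 13/25 (52%) |
| 25:17 | 17/17 (100%) | 13/25 (52%) |
| 25:17 | 15/17 (88.2%) | 15/25 (60%) |

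Under 1:1, a Go with the intervention arm below 50% needs an almost fully retained waitlist. At 25:17 it is impossible, but a Go with that arm in the amber range is not.

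**3. How often.** Exact sums of two independent binomials. The true arm rates are assumptions; the article gives none by arm.

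| True retention (intervention / waitlist) | Arms | P(Go) | P(Go, intervention arm below 50%) | P(Go, observed gap of 20 points or more) |
|---|---|---|---|---|
| 50% / 90% | 21:21 | 49% | 7.7% | 43% |
| 50% / 95% | 21:21 | 65% | 17% | 63% |
| 50% / 95% | 25:17 | 38% | 0 | 37% |
| 55% / 90% | 21:21 | 65% | 6.0% | 52% |
| 73% / 91% | 21:21 | 97% | 0.4% | 36% |
| 73% / 91% | 25:17 | 95% | 0 | 42% |

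The 73% / 91% rows place the arms at the two ends of the 9–27% attrition range cited in Table 2. That range is for whole trials, so using it by arm is itself an assumption. With a true intervention rate of 50%, the true pooled rate passes 70% only if the waitlist exceeds 90%: (0.50 + 0.90)/2 = 0.70.

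**4. What a floor of 50% per arm would do.**

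- At 50% / 95%, 21:21: Go falls from 65% to 48%, and Go with a gap of 20 points or more from 63% to 46%. About a quarter of the large-gap verdicts are removed: (63 − 46)/63 = 27%.
- At 55% / 90%, 21:21: Go with such a gap falls from 52% to 46%.
- At 25:17 the floor never acts through the intervention arm.
- Cost when both arms share a true rate of 75% or 80%: a Go becomes amber in about 0.02% of trials or fewer at 21:21 and about 0.1% or fewer at 25:17.

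**5. Why not a formal test per arm.** With the stated limits and continuity correction, power in a single arm is about 49% at n = 21 and 57% at n = 25. Reaching 80% needs about 42 per arm.

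**The case against.** **The trial's own figures do not point to such extremes.** Table 2 cites attrition of 9–27% and average retention of 80% in earlier trials of this program. With the arms at 73% and 91%, a Go with the intervention arm below 50% is very rare. This stands, and it limits the size of the point. Large observed gaps, however, would still be common in that case.

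**The completion criterion covers it.** Parameter 3 applies to the intervention arm alone and needs more than 60% for green. If completion equalled retention in that arm (an assumption), both would be green in only 19% of trials at 50% / 95% and 21:21, against 65% for retention alone. This stands in part. Completion counts attendance at six or more sessions, not questionnaires returned, and the article does not say how the five verdicts combine.

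**Arm-level loss will be visible anyway.** Dropout is recorded in both arms and reporting is to follow CONSORT with its pilot extension. True for the report, but the progression rule does not use the information.

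**A stronger reading.** A reader might infer that the rule generally lets the whole trial proceed with the intervention arm in the red zone. The documents do not support that. It depends on which of the two stated allocations applies, it needs a nearly complete waitlist, and Go here is the verdict on one of five parameters.

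**Conclusion.** The point holds in a limited form. The retention rule pools both arms although its stated purpose is unbiased data for a comparison between them. Under 1:1 allocation (21:21 or 25:25) it can return Go with the intervention arm below the trial's own red limit. Under 25:17 it cannot, but it can return Go with an arm in the amber range and a large gap.

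The size depends on unknown arm-level retention: at an assumed 50% / 95% a Go occurs in 65% of trials at 21:21 and 38% at 25:17, while at 73% / 91% a Go with the intervention arm below 50% has probability 0.4% or less.

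Nothing stated is miscalculated on this point, and the pooled rate matches the pooled sample-size basis. It is a cheap improvement to a stated decision rule.

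**What to change.** Keep the pooled limits and the sample size, and make three changes.

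1. In Table 2, parameter 1, add that green also requires neither arm's observed retention to be below 50%; otherwise the parameter is amber.
2. Show retention by arm and the between-arm difference beside the verdict, as a description without a test. This is needed because the floor catches only extreme cases. A fixed gap limit would be noisy: at a true 80% in both arms (21:21), a Go still comes with an observed gap of 20 points or more in about 7% of trials.
3. Reconcile section 2.1 (1:1) with section 2.7 (25 of 42), since the arm sizes decide what the pooled rule can hide.

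The cost is a sentence or two, using dropout data already to be recorded by arm. The downside is an occasional extra Amend: about 0.1% of trials or fewer when both arms truly retain the same 75% or 80%.

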4. Feasibility of Program Acceptability *Does an appropriate number of families from the intervention arm rate the BaP program acceptable?*	GREEN ZONE (Go—Proceed with full RCT)	>75%	Program acceptability is an important criterion in considering if the BaP program will be well received in the Portuguese community Program acceptability will be measured using the treatment acceptability rating scale (TARS) A total score of 27 or more equates to ratings of “Quite a lot” or “A great deal” on each item Previous trials of the BaP program found that an average of 98.5% of participants had total scores ≥ 27 [19] A conservative threshold of 75% will be used
	AMBER ZONE (Amend—Proceed with changes)	45–75%	
	RED ZONE (Stop—Do not proceed unless significant changes are made)	<45%	
5. Feasibility of Program Fidelity *Can the BaP intervention be delivered as planned?*	GREEN ZONE (Go—Proceed with full RCT)	>70%	For the BaP program, 75% fidelity is considered appropriate, which would mean that six out of eight sessions were delivered as planned Fidelity estimates serve as indicators to identify deviations from the designed intervention delivery, exposing potential issues like methodological challenges and variances with local contexts [44] Increasing fidelity correlates with improved outcomes [44] Conservative estimates of fidelity rates are used because this is the first time the BaP program will be tested in a Portuguese context, and thus, cultural and linguistic factors can significantly impact fidelity
	AMBER ZONE (Amend—Proceed with changes)	40–70%	
	RED ZONE (Stop—Do not proceed unless significant changes are made)	<40%	

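### The acceptability cut-off of 27 does not match its stated meaning on a 12-item scale, and no total score can ensure a rating on each item

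*Protocol article*

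**What the plan says.** Acceptability is the fourth of five feasibility parameters in Table 2 (section 2.7). Its question is: "Does an appropriate number of families from the intervention arm rate the BaP program acceptable". The zones are green above 75%, amber 45–75% and red below 45%, and the table adds: "A conservative threshold of 75% will be used".

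Whether a respondent counts as finding the program acceptable depends on the TARS total. Table 2 explains the cut-off thus: "A total score of 27 or more equates to ratings of" 'Quite a lot' or 'A great deal' on each item. It supports the cut-off with earlier trials of the program, which "found that an average of 98.5% of participants had total scores ≥ 27".

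Section 2.6.1 describes the scale: "It comprises 12 tailored items in which parents will report on satisfaction with intervention delivery". Neither section gives the numerical codes of the response categories, or says that fewer than 12 items enter the total.

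**The concern.** The cut-off is defined twice, once as a number and once in words, and on the scale described in section 2.6.1 the two definitions select different parents. Section 2.8.3 uses these zones to decide whether to progress to a full RCT. If the analyst applies the number, one set of parents counts as satisfied; if the analyst applies the words, another does. A choice made after the data are in would weaken a rule that is meant to be fixed in advance. The comparison with the earlier 98.5% also holds only if the same items are scored in the same way.

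**Working it through.** **Inputs**
- Number of items: 12 (section 2.6.1).
- Cut-off: total of 27 or more, said to mean one of the two named ratings on each item (Table 2, parameter 4).
- Item coding: not given. Assumption: four categories with consecutive whole-number codes, the same for all items, the two named ratings being the top two. Both usual codings, 0–3 and 1–4, are shown.

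**Step 1. Can 27 be reproduced?** If every item must reach code q, the lowest qualifying total on k items is k × q.
- With k = 12: 27/12 = 2.25, not a whole-number code.
- With q = 2 (coding 0–3): 27/2 = 13.5 items, impossible.
- With q = 3 (coding 1–4): 27/3 = 9 items.

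Under these codings, 27 is reproduced only by nine scored items coded 1–4.

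**Step 2. Distance from the stated meaning with 12 items**

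| Coding (assumed) | Code for 'Quite a lot' | Lowest total, all 12 items at that rating | 27 relative to it |
|---|---|---|---|
| 0–3 | 2 | 12 × 2 = 24 | 3 above |
| 1–4 | 3 | 12 × 3 = 36 | 9 below |

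**Step 3. Who passes at 27 with 12 items**
- Coded 0–3: a parent answering 'Quite a lot' throughout scores 24 and fails, although the description is met. A parent with nine items at 3 and three at 0 scores 9 × 3 + 3 × 0 = 27 and passes, although three items are at the lowest category.
- Coded 1–4: one item at 4, one at 3 and ten at 2 give 4 + 3 + 20 = 27. That parent passes with only two of 12 items at 'Quite a lot' or better.

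**Step 4. Does the nine-item reading settle it?** Only in part. On nine items coded 1–4, one item at 4, one at 2 and seven at 3 give 4 + 2 + 21 = 27. The parent passes with one item below 'Quite a lot'.

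This is general. With k items, the lowest total that meets the description is kq. The highest total with one item just below it is (k − 1)(q + 1) + (q − 1) = kq + k − 2. A total equivalent to the description would have to be no more than kq and also more than kq + k − 2, which is impossible for two or more items. For 12 items the two values are 24 and 34 (coded 0–3) or 36 and 46 (coded 1–4); for nine items coded 1–4 they are 27 and 34.

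**The case against.** The strongest defence is that 27 is an inherited cut-off: Table 2 reports earlier results at the same value, so the number may be right and only the item count, or the account of which items are scored, may be loose. With nine scored items coded 1–4, 27 is exactly an average of 'Quite a lot', and the number would not change. This stands as an explanation, and it is why the point is not that 27 itself must be wrong. It does not remove the conflict, because the article gives both the item count and the meaning of the cut-off. Nor does it rescue the claim about each item (step 4). A separate analysis plan might give the coding, but the conflict is in what the article states, not in what it omits.

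A reader might infer more, and the document does not support it:
- *That green is too easy to reach.* This follows if 12 items are summed on 1–4 coding. On 0–3 coding, 27 is 3 points above the all-'Quite a lot' total. The coding is unknown, so the direction is too.
- *That only responders are counted.* Section 2.6.1 says the scale "will be completed by the participants from the experimental group post-intervention". That fixes who fills it in and when, not the denominator, and the question in Table 2 can be read as covering all families in the arm. Making all families the denominator is also debatable: retention is a parameter of its own, so dropout would count twice.
- *That there are too few raters.* The plan states: "Feasibility of program acceptability (Rul = 0.45 and Gll = 0.75)—19 participants (intervention arm". That figure reproduces with its "one-tailed, one-sample binomial test based on normal approximation (with continuity correction) with α = 0.05" at 80% power: n = [(1.645 × √(0.45 × 0.55) + 0.842 × √(0.75 × 0.25))/0.30]² = 15.54, and with the correction 15.54/4 × [1 + √(1 + 2/(15.54 × 0.30))]² = 18.73, rounded up to 19. The planned 25 in the arm at the 80% retention cited in Table 2 give 20 raters, above 19, with power 0.83 by the same method. A shortfall appears only under less favourable assumptions, such as 70% retention (25 × 0.70 = 17.5).

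**Conclusion.** The point holds as an internal contradiction in a stated decision threshold. For 12 equally coded items, 27 is not the total at which every item reaches 'Quite a lot'. It is 3 points too high under 0–3 coding or 9 points too low under 1–4 coding, and both codings are assumptions. Either the item count, the scored subset or the cut-off is misstated; the document does not show which. Separately, and whatever the number of items, a total cannot carry the meaning that Table 2 gives it, because it allows low items to be offset by high ones.

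The effect on the acceptability percentage cannot be sized, since no distribution of item answers is given, and its direction cannot be determined. The conclusion does not extend to the denominator, the number of raters or the sample size of 19.

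**What to change.** Reconcile section 2.6.1 with Table 2, parameter 4, before the data are examined:
1. State which TARS items are scored and the numerical code of each response category.
2. Choose one definition. Either set the cut-off to the number of scored items times the code for 'Quite a lot' and describe it as an average rating of at least 'Quite a lot', or define acceptability directly as every scored item at 'Quite a lot' or above. If nine items coded 1–4 are scored, the first option keeps 27 and changes only the wording.
3. Tabulate the share with 27 or more, scored as in the earlier trials, as a secondary result, so that the comparison with 98.5% is kept.

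The cost is a text change and one extra tabulation. The acceptability rate may differ somewhat from the one that 27 would have given.
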